## Methods

### Study Design and Setting

The Vision-T1D study is a prospective cohort designed to screen children aged 2-18 years who have an FDR with T1D (index case). Participants are recruited from the University Diabetes Centre (UDC) at King Saud University Medical City (KSUMC) in Riyadh, Saudi Arabia. The diagnosis of T1D in index cases is based on the American Diabetes Association criteria [22], and T1D classification is determined by a clinical diagnosis from a specialized endocrinologist, with or without confirmatory islet autoantibodies testing. Exclusion criteria included index cases diagnosed with other forms of diabetes and non-Saudi children due to different ethnic and genetic backgrounds.

### Ethical Considerations

The study was approved by the Institutional Review Board of King Saud University Ethics Committee (approval: E-248566). The pilot phase began in May 2024, with 1 year dedicated to recruitment and screening. All procedures were conducted in accordance with the ethical standards of the Declaration of Helsinki and national research ethics guidelines.

Informed consent was obtained from all participants or their legal guardians prior to data collection. Privacy and confidentiality were maintained according to GCP standards. Participants identified as at risk or presymptomatic for T1D will enter a 4-year clinical follow-up phase, culminating in a total study duration of 5 years.

Participants did not receive financial compensation for participation. However, We have received funding for the project as described in the acknowledgment section.

### Study Process and Interventions

The VISION-T1D study consists of 3 well-structured phases: screening, results communication and counseling, and long-term clinical follow-up. Each phase is designed to provide tailored interventions, ensuring appropriate care, monitoring, and education for children and their families (Figure 1).

**Figure 1 figure1:**
[figure not shown]
The study flowchart. CGM: continuous glucose monitoring; HbA_1c_: hemoglobin A_1c_; MODY: maturity-onset diabetes of the young; OGTT: oral glucose tolerance test; T1D: type 1 diabetes; T2D: type 2 diabetes.

#### Phase 1: T1D Screening

Families are recruited and scheduled for an enrollment and screening visit, where they receive comprehensive counseling about participation and education on T1D screening. Upon obtaining informed consent and assent, participants undergo baseline assessments, including completion of questionnaires and the collection of blood samples for islet autoantibody testing. Optional genetic screening for HLA phenotyping and GRS analysis is also offered to evaluate genetic predisposition to T1D. To enhance recruitment, a home testing option is provided, allowing families to conveniently perform finger-prick testing and data collection at home.

#### Phase 2: Results Communication, Education, and Metabolic Staging

After screening results are available, a research physician reviews the findings. Participants who test positive for islet autoantibodies are invited to a follow-up visit that includes personalized counseling, targeted educational interventions, and additional metabolic staging to determine their T1D stage. Participants with negative islet autoantibody results are notified by the research staff and are invited for repeat autoantibody screening at the conclusion of the long-term follow-up period (approximately 4-5 years later).

#### Phase 3: Long-Term Clinical Follow-Up

Participants identified as having presymptomatic T1D (stage 1 or 2) or those at risk based on autoantibody markers enter a 4-year clinical follow-up phase. During this period, regular monitoring of disease progression is conducted through metabolic assessments and psychological evaluations. Participants receive continuous support tailored to their risk level and diagnosis.

This systematic, 3-phase approach ensures that participants receive appropriate care, counseling, and monitoring based on their screening outcomes.

### Phase 1: T1D-Screening Procedures and Data Collection

#### Recruitment and Enrollment

Active and passive recruitment strategies are used. Research staff identified potential participants by reviewing patient lists from KSUMC diabetes clinics and pediatric endocrinology inpatient records. Recruitment materials, including advertisements with QR codes, are shared via the UDC and on social media platforms. The QR codes were linked to an introductory video explaining the study and eligibility criteria, along with a contact submission form. Families who decline participation are asked about the reason for refusal.

#### Informed Consent

Eligible families are scheduled for T1D-screening visits, where informed consent and assent are obtained. A comprehensive educational approach was developed to ensure participants receive standardized information and fully understand the T1D-screening process. This included an animated video and an educational booklet. The video, in Arabic, explains the screening program and key concepts, such as T1D pathophysiology, its stages, and clinical presentation. It emphasizes the benefits of early detection in preventing DKA and improving long-term outcomes; outlines the screening process; and provides an overview of current and emerging T1D treatments, including insulin therapy and disease-modifying interventions. The educational booklet complemented the video, using infographics to illustrate T1D pathophysiology, stages, symptoms, and benefits of screening. It also outlined study expectations and provided key study contact information.

#### Intervention: T1D Screening

##### Islet Autoantibodies Screening

The program uses antibody detection by agglutination–polymerase chain reaction (ADAP) assay, a cutting-edge technology developed by Enable Biosciences. The assay measures islet autoantibodies [23-27], including insulin autoantibodies, glutamic acid decarboxylase autoantibodies, IA-2 autoantibodies, and zinc transporter 8 autoantibodies, using dried blood spots on filter paper. The ADAP assay offers notable advantages over other assays for large-scale analysis, such as cost-effectiveness, high sensitivity and specificity, and minimal sample volume requirements. These features make it suitable for large-scale applications, including home testing [25-27].

##### Genetic Risk Screening

This pilot study integrated optional HLA phenotyping and GRS testing to deepen the understanding of T1D pathogenesis in the Saudi population. Analyses will be conducted by Enable Biosciences, the Barbara Davis Center for Childhood Diabetes, and delegates [28,29]. These tests are used for research purposes only.

###### HLA Phenotyping

Testing focuses on identifying high-risk HLA genotypes associated with T1D, particularly variants in the HLA region (MHC class II alleles), which account for over 50% of T1D heritability [13]. This approach aims to provide insights into T1D risk associations in the Saudi population, especially in participants with negative islet autoantibodies. HLA typing is performed using oligonucleotide probes for *HLA-DRB1*, *DQA1*, and *DQB1* alleles as previously described [30].

###### GRS Testing

The GRS aggregates the cumulative contribution of multiple genetic variants into a single score estimating an individual’s genetic predisposition to T1D [29,31-33]. This study uses GRS2, an advanced version that incorporates HLA haplotypes, non-HLA loci, and interactions between HLA variants [34]. Testing is conducted using a Kompetitive allele-specific polymerase chain reaction (PCR) assay, as described earlier [35,36]. The Kompetitive allele-specific PCR assay is a cost-effective and efficient alternative to the traditional DNA array and imputation-based methods. It successfully genotypes 60 of the 67 single nucleotide polymorphisms in GRS2, with the remaining single nucleotide polymorphisms excluded due to genotyping challenges. This study represents one of the first applications of GRS2 in FDRs of patients with T1D and the first validation of its use within the Saudi population.

##### Specimen Collection

Blood samples are collected via fingerstick or venous sampling onto dried blood spot filter paper, based on participant preference. For families opting for home testing, parents collect sample cards and detailed instructions from the clinic, perform the testing at home, and return the samples for processing. All collected samples are stored at –80 °C before being batched and shipped to the United States for analysis.

#### Measures

##### Demographics and Clinical Characteristics

Families complete a self-administered questionnaire upon enrollment to collect baseline demographics and clinical characteristics. Information includes the age, sex, medical history, and current medications of the participating child, as well as family demographics such as parental age, marital status, number of siblings, education levels, family income, residential region, and family medical history focused on diabetes or autoimmune diseases among FDR and any self-reported parental comorbidities. For the index case with T1D, the questionnaire captures clinical details, including the relationship to the participant, age at diagnosis, current age, insulin regimen, history of DKA at onset or recurrent DKA, and diabetes-related complications. If multiple FDRs have T1D, similar information is collected for each.

##### Clinical T1D Screening

Participants are screened for overt diabetes symptoms, such as polyuria, polydipsia, polyphagia, and unexplained weight loss. Research staff conduct point-of-care hemoglobin A_1c_ (HbA_1c_) and random blood glucose tests if any symptoms are reported. Participants with abnormal blood sugar levels are referred to a research physician for further evaluation, which may include an oral glucose tolerance test (OGTT) and counseling. Those meeting the diagnostic criteria for stage 3 T1D will receive standard medical care and education for new-onset diabetes.

##### Health Literacy

The Single-Item Literacy Screener tool evaluates parental health literacy using a 5-point Likert scale. A score of 4 or higher indicates adequate health literacy, while a score of 3 or lower suggests limited literacy [37-39].

##### T1D-Screening Acceptability Assessment Scale

This self-administered tool evaluates caregivers’ acceptability of the T1D-screening program through 10 items rated on a 5-point Likert scale. Domains include affective attitude, the ethicality of the screening, perceived effectiveness, self-efficacy, opportunity costs, communication, burden, and general and cultural acceptability. Total scores range from 10 to 50, with higher scores indicating greater acceptability [40].

##### Psychological Measures

A set of validated Arabic tools assess caregiver stress, anxiety, depression, and quality of life at baseline, after results disclosure, and during long-term follow-up.

###### Anxiety Symptoms

The Generalized Anxiety Disorder 7-item scale screens for generalized anxiety over the past 2 weeks using a 4-point Likert scale. A score of 8 or more indicates possible generalized anxiety disorder, with 92% sensitivity and 76% specificity [40,41].

###### Depressive Symptoms

The Patient Health Questionnaire-9 screens for depression. A score of more than 10 suggests possible major depressive disorder, with a sensitivity and specificity of 88% [42-44]. Research staff will screen responses indicating suicidal ideation and prompt immediate referral to emergency care.

###### Health-Related Quality of Life

The EQ-5D-5L tool from the EuroQol Group measures health across 5 dimensions—mobility, self-care, usual activities, pain or discomfort, and anxiety or depression—each rated on 5 levels. The EuroQol Visual Analogue Scale allows participants to rate their overall health from 0=worst to 100=best [45]. The results are scored using a value set specific to Saudi Arabia, providing a comprehensive quality of life score [46].

###### Distress

The Subjective Units of Distress Scale measures anxiety and discomfort on a 0-100 scale, with higher scores indicating greater distress. The Subjective Units of Distress Scale is widely used and validated in clinical settings for assessment and monitoring of changes over time [47-49].

##### Anthropometric Measurements

Baseline assessments will include weight, height, BMI, and self- or parental-reported pubertal status [50].

### Phase 2: Result Disclosure, Education, and Metabolic Staging

#### Results Disclosure

Participants receive written reports explaining the results, estimated risk of progression, long-term follow-up recommendations, and key contact information. The process of sharing results varies based on screening outcomes:

##### Participants With Negative Results

Families of participants who test negative for islet autoantibodies are contacted by the research staff to receive their results report. They are instructed to contact the research team if T1D develops in the future and are invited for repeat antibody testing at the end of the follow-up phase.

##### Participants With Positive Results

Families of participants who test positive for multiple islet autoantibodies are invited to a one-to-one counseling visit with a research physician to discuss the result, followed by a group education and metabolic staging to determine their T1D stage.

##### Participants With Equivocal Results

Families of participants with a single autoantibody are invited for a one-to-one counseling session with a physician to discuss the result. They then join the same group educational session as those with positive results.

#### Genetic Testing Disclosure

Genetic testing results are shared with families only upon request to avoid unnecessary alarm given the elevated baseline risk among FDRs and the lack of validated Saudi population–based genetic risk estimation. When shared, these results are presented in a dedicated educational session designed to help families understand the complexities of genetic predisposition to T1D.

#### Educational Curriculum for Participants With Positive or Equivocal Results

The educational curriculum was developed based on a comprehensive robust educational framework and expertise [51]. It is delivered in small group sessions by experienced endocrinologists, diabetes educators, and dietitians. The curriculum covers key topics such as T1D pathophysiology, disease progression stages, and the importance of early detection. Participants learn to identify their specific stage and risk of progression and recognize factors that influence clinical diabetes onset. The curriculum highlights insulin’s role as the primary treatment for clinical T1D (stage 3), addressing common concerns and misconceptions. Participants are also trained to monitor their condition by recognizing early T1D symptoms, performing blood glucose checks, interpreting results, and determining when insulin therapy or medical advice is needed.

The program underscores nonpharmacological strategies for reducing the risk of T1D progression through healthy eating and lifestyle modifications and provides an overview of current and future T1D research. The psychological and emotional aspects of receiving T1D screening results are also addressed, and access to support is provided.

#### Psychological Support

The psychological and emotional impact of T1D risk disclosure is carefully addressed throughout the process. Families experiencing significant psychological burdens are offered counseling sessions and access to professional psychological support. Additionally, all families can self-refer to these services as needed. These measures are designed to alleviate stress, promote resilience, and ensure families feel supported during the follow-up period.

#### Metabolic Staging

Participants with multiple positive islet autoantibodies undergo metabolic staging to determine their T1D stage. This includes HbA_1c_ measurement, fasting glucose, 2-hour OGTT, or continuous glucose measurement (CGM) if OGTT is not feasible.

##### OGTT Measurement

Performed after an overnight fast of at least 8 hours. Participants consume a glucose solution dosed at 1.75 g/kg (up to 75 g). Serum glucose levels are measured at fasting baseline and 120 minutes after ingestion.

##### HbA_1c_ Measurement

Serum samples will be processed in the laboratory per American Diabetes Association–recommended standards.

##### CGM Measurement

Used as an alternative for participants unable or unwilling to complete an OGTT. CGM glucose profiles over a 2-week period will be reviewed for staging.

### Phase 3: Long-Term Monitoring and Clinical Follow-Up

#### Monitoring for Disease Progression

Participants with positive single or multiple autoantibodies will enter a 4-year follow-up phase. During this period, regular assessments are performed to monitor T1D disease progression, track time to clinical onset, and observe any changes in metabolic staging. Monitoring intervals vary by stage and risk level [18,20]. Participants progressing to stage-3 T1D will transition to standard care.

##### Self-Monitoring of Blood Glucose

All participants with multiple positive islet autoantibodies results will be instructed to perform self-monitoring of blood glucose testing at home twice over a 2-week period after receiving their results, including one fasting test and one 2-hour postprandial test after a heavy meal. This testing should be repeated every 1-3 months and during any illness. Participants will be provided with contact information and guidance on when to seek medical advice.

##### Stage-1 Monitoring

Participants categorized as stage-1 T1D (positive autoantibodies with normal glycemia) will have clinic visits every 6 months for HbA_1c_ and random glucose testing. An OGTT or CGM will be performed every 24 months or earlier if there is a 10% or more rise in HbA_1c_ from baseline.

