##### Stage-2 Monitoring

Participants categorized as stage-2 T1D (positive autoantibodies with dysglycemia) will have more frequent clinic visits every 3 months for HbA_1c_ and glucose testing. An OGTT or CGM will be performed annually or sooner if there is a 10% or more rise in HbA_1c_ from baseline.

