#### T1D Progression Rate

The annual progression rate to stage-3 T1D will be tracked in participants testing positive during the follow-up phase (phase 3) and categorized based on their initial stage.

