#### Statistical Analysis

Descriptive statistics will report continuous data as mean (SD) for normally distributed variables and categorical data as frequency and percentage (N, %). Feasibility metrics and T1D stages will also be summarized as percentages.

To evaluate the psychological effects of T1D screening on caregivers, pre- and postscreening levels of anxiety, depression, and distress will be compared using paired 2-tailed *t* tests or Wilcoxon signed-rank tests, depending on data distribution. The effectiveness of educational counseling will be analyzed similarly, comparing pre- and postintervention test scores. Longitudinal changes in the psychological measures will be evaluated using repeated-measures ANOVA or mixed effects models to track patterns over time.

For participants with presymptomatic T1D, progression rates to stage 3 will be analyzed using Kaplan-Meier survival analysis. Time to event will be calculated from screening age to age at stage-3 T1D diagnosis or last follow-up. Cox proportional hazards models will assess factors associated with disease progression, such as baseline autoantibody titers, genetic risk scores, and demographic variables.

At the 1-year follow-up, cost-effectiveness will be assessed by reporting total costs for all screened participants, cost per child screened, and cost per case detected. The incremental cost-effectiveness ratio calculations will compare outcomes for screened children with controls diagnosed with stage-3 T1D in the general population. The incremental cost-effectiveness ratio will incorporate potential benefits, such as reduced DKA incidence and improved HbA_1c_ levels, while adjusting for control characteristics like age and FDR status.

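### Stage-1 children have clinic tests for stage 3 half as often as stage-2 children, so annual rates by initial stage, timed to diagnosis, partly follow the testing calendar

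*Protocol article*

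**What the plan says.** All references are to the protocol article.

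- **Stage-1 Monitoring:** children "will have clinic visits every 6 months" for HbA1c and random glucose. "An OGTT or CGM will be performed every 24 months or earlier", the earlier test being prompted "if there is a 10% or more rise in" HbA1c from baseline.
- **Stage-2 Monitoring:** children "will have more frequent clinic visits every 3 months" for HbA1c and glucose. "An OGTT or CGM will be performed annually or sooner", with the same HbA1c prompt.
- **Self-Monitoring of Blood Glucose:** every child with multiple autoantibodies does home checks, whatever the stage. "This testing should be repeated every 1-3 months and during any illness".
- **Prevalence of Presymptomatic T1D at Screening:** stage 3 is defined by thresholds on HbA1c, fasting glucose, 2-hour OGTT or CGM.
- **T1D Progression Rate:** "The annual progression rate to stage-3 T1D will be tracked in participants testing positive during the follow-up phase (phase 3"), broken down by initial stage.
- **Statistical Analysis:** for presymptomatic children, "progression rates to stage 3 will be analyzed using Kaplan-Meier survival analysis". Time runs from age at screening to age at stage-3 diagnosis or last follow-up, and Cox models look for factors linked to progression.

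The limitations in the Discussion do not mention the unequal testing.

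**The concern.** A symptom-free child enters the data as stage 3 only when a test is done. Both clinic intervals differ between the stages by a factor of exactly two (24/12 and 6/3). An onset visible only on OGTT or CGM, without symptoms or an HbA1c rise large enough to prompt an earlier test, cannot be recorded in a stage-1 child before month 24, nor between months 24 and 48. In a stage-2 child it can be recorded each year.

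The reported quantity is an annual rate by initial stage, with the date of detection used as an exact event time. Part of the year-by-year pattern, and part of any stage difference read between the shared test dates, is then produced by the calendar. Natural history, including time to clinical onset, is a stated secondary objective.

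**Working it through.** The article gives no progression rate, event count or power for this outcome, so there is no figure of its own to reproduce. The check asks what the two schedules would record if the disease behaved identically in both stages.

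**Inputs**
- OGTT/CGM interval 24 versus 12 months; HbA1c interval 6 versus 3 months (Stage-1 and Stage-2 Monitoring).
- Follow-up 4 years (Monitoring for Disease Progression).
- Hazard, an assumption: constant and equal in both stages. From the Background figure of 84% at 15 years, λ = -ln(0.16)/15 = 0.122 per year. Range tried: 0.08 to 0.25.
- Share *s* of onsets visible only on OGTT/CGM, an assumption varied from 0 to 100%. The other onsets are found at the next HbA1c visit or at once.

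**True cumulative risk**, 1 - exp(-λt): 11.5%, 21.7%, 30.7% and 38.7% at years 1 to 4.

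**Recorded cumulative risk.** At whole years the stage-2 schedule reproduces the true values. On the stage-1 schedule, OGTT-only onsets are known only up to the last even year:
- Year 1: *s* × 0 + (1 - *s*) × 11.5%
- Year 3: *s* × 21.7% + (1 - *s*) × 30.7%

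| | Year 1 | Year 2 | Year 3 | Year 4 |
|---|---|---|---|---|
| Stage-2 schedule, any *s* | 11.5% | 21.7% | 30.7% | 38.7% |
| Stage-1 schedule, *s* = 25% | 8.6% | 21.7% | 28.4% | 38.7% |
| Stage-1 schedule, *s* = 50% | 5.8% | 21.7% | 26.2% | 38.7% |
| Stage-1 schedule, *s* = 100% | 0% | 21.7% | 21.7% | 38.7% |

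**Yearly rates per 100 person-years** (simulation, 1,000,000 children per schedule, equal hazard):
- *s* = 100%: 0 / 21.6 / 0 / 21.7 for stage 1, about 11.5 every year for stage 2.
- *s* = 50%, the rest found at HbA1c visits: 5.9 / 17.1 / 5.9 / 17.2 against about 11.8.
- *s* = 25%, half found at once and a quarter at HbA1c visits: 8.9 / 14.8 / 9.0 / 14.9 against 12.0.

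**Average rate over 4 years.** Both schedules record the same 38.7% by month 48, so only person-time differs. For *s* = 100%:
- Stage 1: 2 × (1 + 0.783) = 3.57 person-years per child, and 0.387/3.57 = 10.8 per 100.
- Stage 2: 1 + 0.885 + 0.783 + 0.693 = 3.36, and 0.387/3.36 = 11.5 per 100.
- Ratio 0.94.

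In the 50% and 25% scenarios above, the ratio is 0.96 and 0.98. Over hazards of 0.08 to 0.25 and all detection shares it runs from 0.89 to 1.00.

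**If follow-up ends before month 48.** Take 45 months, an assumption, with onsets other than OGTT-only ones dated as they occur. The true risk is 1 - exp(-0.122 × 3.75) = 36.75%. The last OGTT/CGM was at month 24 in stage 1 and month 36 in stage 2.
- *s* = 25%: 0.25 × 21.7 + 0.75 × 36.75 = 33.0% against 0.25 × 30.7 + 0.75 × 36.75 = 35.2%.
- *s* = 50%: 29.2% against 33.7%.
- *s* = 100%: 21.7% against 30.7%.

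**The case against.** **Other routes to detection.** Home glucose checks apply equally to both stages, and clinic visits include a glucose test. A stage-1 child found to be dysglycemic would presumably move to the denser schedule before reaching stage 3. All of this stands. It means that *s* may be well below 100%, and that "half as often" is true of clinic tests only.

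**Small bias against sampling error.** Suppose, generously, that all of the article's 5-15% seropositive among 1300 were multiple-positive. That gives 65-195 children and, at 38.7%, about 25-75 events. The 95% limits on one pooled rate are then a factor of exp(1.96/√75) = 1.25 to exp(1.96/√25) = 1.48. This exceeds the 4-year bias and stands for the 4-year rate. It does not excuse a systematic low-high-low-high pattern in the yearly rates.

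**No formal stage contrast.** The article only breaks rates down by initial stage, and its Cox examples are titers, genetic scores and demographics. Time to diagnosis under the programme is a coherent endpoint, and risk-based visits are a deliberate choice. These points also stand. But annual rates shown side by side by stage will be compared.

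**Left to the analysis plan.** A separate plan may handle interval censoring. However, the article itself fixes the outcome, the breakdown, the event time and the method, and together these give the pattern above.

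**The HbA1c prompt.** A reader might infer that the 10% prompt contradicts the staging bands. It does not. A stage-1 child (below 5.7%) who reaches 6.5% has risen by at least 6.5/5.7 - 1 = 14%, so the prompt has been met. A stage-2 child who reaches 6.5% is seen at the 3-monthly visit. A relative prompt and absolute bands can coexist.

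**Conclusion.** The point holds for year-by-year rates and for the shape of the stage-1 curve. With equal hazards of 0.122 per year and an OGTT-only share of 25-50%, recorded year-1 risk is about 6-9% in stage 1 against 11.5% in stage 2, with a matching excess in years 2 and 4. The hazard and the share are assumptions, and the check ignores re-staging, so the true size may be smaller.

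A reader might infer that the schedule could create a large stage-2 versus stage-1 difference. The documents do not support that. At the 3-year mark, close to the worst point, the ratio of cumulative hazards is ln(1 - 0.307)/ln(1 - 0.284) = 1.1 for a 25% share and ln(1 - 0.307)/ln(1 - 0.262) = 1.2 for 50%. Over the full 4 years the stage-1 to stage-2 rate ratio is about 0.94-0.98, and with full attendance there is no difference at 24 or 48 months.

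That reassurance depends on the month-48 test being done. The study is set at 5 years including a year of recruitment, and samples are batched and sent abroad, so late entrants may fall short of it.

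**What to change.** Leave the clinical schedule unchanged.

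1. **Statistical Analysis:** define onset as lying between the last assessment that did not show stage 3 and the first that did. Replace Kaplan-Meier and Cox by a Turnbull estimate and an interval-censored proportional hazards model. State which test sets the lower limit: a normal HbA1c does not exclude an onset visible only on OGTT/CGM, so for such an onset the limit is the last negative OGTT or CGM.
2. **T1D Progression Rate:** compare initial stages by cumulative progression at 24 and 48 months, where the two schedules coincide, instead of by annual rates.
3. **Data collection:** record for each diagnostic test whether it was scheduled, triggered or symptom-driven. This is hard to recover afterwards, so the field should be added while follow-up is running.

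The cost is revised analysis wording and one data field. The downside is slightly wider intervals and no annual comparison between stages.
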